##### Candidate Mechanisms

Measures have been selected that map directly onto hypothesized mechanisms of change and known predictors of relapse. Mechanisms of service user benefit are operationalized as improvements in personal recovery, empowerment, and utilization of social support.

Recovery and self-efficacy: Questionnaire for Personal Recovery [67] and the General Self-Efficacy Scale [68] will be completed by service user participants.Social and interpersonal context: Psychosis Attachment Measure [69] and Perceived Criticism and Warmth Measure adapted from the Perceived Criticism Measure (PCM) [70] will be completed by service user participants.

#### Carer Outcomes

The Involvement Evaluation Questionnaire [71] will be completed as a measure of carers worrying, tension, urging, and supervision. A carer PCM adapted from the PCM described above will be used as a measure of carers’ perspectives on relationship quality.

We will also assess Carer Health Economic Outcomes using a purposively designed RUQ, time cost questionnaire, the EQ-5D-5L, and the CarerQol-7D.

#### Care Coordinator Outcomes

Participants care coordinators will complete the Service Engagement Scale [72].

### Process Evaluation

In line with recent MRC Guidance on process evaluation of complex interventions [73], we will produce a logic model for the EMPOWER intervention and conduct a process evaluation. The process evaluation will be used to explore the ways in which EMPOWER may operate to produce outcomes. Specifically, it will focus on intervention fidelity, exposure, reach, context, recruitment, retention, and contamination, as well as the acceptability of study procedures. We will interview service users, carers, mental health staff, and research staff to ensure a multiperspective understanding of the intervention. We will publish the protocol for the process evaluation elsewhere.

### Sample Size

No formal sample size calculation is appropriate for this pilot phase. The proposed sample size of up to 120 service users across 40 care coordinators in 8 CMHSs is deemed to be sufficient to establish feasibility and obtain parameters (including the relevant ICCs for the cluster design) to inform the design and size of a future definitive, pragmatic, multicenter, and multinational cRCT.

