**Methods:**

We will randomize CMHSs to EMPOWER or TAU. We aim to recruit up to 120 service user participants from 8 CMHSs and follow them for 12 months. Eligible service users will (1) be aged 16 years and above, (2) be in contact with local CMHSs, (3) have either been admitted to a psychiatric inpatient service or received crisis intervention at least once in the previous 2 years for a relapse, and (4) have an International Classification of Diseases-10 diagnosis of a schizophrenia-related disorder. Service users will also be invited to nominate a carer to participate. We will identify the feasibility of the main trial in terms of recruitment and retention to the study and the acceptability, usability, safety, and outcome signals of the EMPOWER intervention. EMPOWER is a mobile phone app that enables the monitoring of well-being and possible EWSs of relapse on a daily basis. An algorithm calculates changes in well-being based on participants’ own baseline to enable tailoring of well-being messaging and clinical triage of possible EWSs. Use of the app is blended with ongoing peer support.

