We aim to approach and consent on an average of 3 participants per care coordinator (giving a total of up to 120 potential participants). Following consultation with the independent Data Management and Ethics Committee (DMEC) and the Study Steering Committee (SSC) in May 2018, these recruitment objectives were amended to 86 participants. This was because of a number of challenges to recruitment including (1) temporary suspension of the study to apply for registration with the MHRA, which delayed start up to recruitment, (2) comprehensive and detailed screening of all potential trial participants, (3) delays arising from care coordinators approaching potential participants, and (4) high rates of turnover among care coordinators. Following independent methodological and statistical advice, there was clear guidance that the original feasibility aims will be met by the trial, and this change to recruitment targets was approved by the funders. After completing baseline assessments on all consenting service users in care coordinators’ and CMHSs’ caseload, the Clinical Trials Unit (CTU) at CHaRT will conduct randomization of the CMHSs. For Australia, with just 2 clusters, this will be by simple randomization by the CTU. For Glasgow, with 6 clusters, the CTU will create 3 pairs of teams based on similarity of the catchment area in terms of social deprivation (Carstairs) score or CMHS type (eg, early intervention service). The CTU will randomly allocate one member of the pair to the intervention, and the remaining member will be allocated to control.

We will explore in this pilot phase the best method of randomly allocating the clusters in the full trial, specifically to establish what matching factors (if any, and/or if matching at all is appropriate, methodologically) are suitable. Any violations of the study protocol will be recorded and reported to the Research Ethics Committee, SSC, and the independent DMEC.

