### Statistical Analysis

A full statistical analysis plan will be written before (and published on the CHaRT website) any analysis is being undertaken. All analyses will be carried out using the intention-to-treat principle with data from all participants included in the analysis including those who do not complete the intervention. Every effort will be made to follow up all participants in both arms for research assessments. The analysis will follow the guidelines of the CONSORT statement for clustered randomized trials and recommendations for the analysis of clustered randomized trials when presenting and analyzing the data. Here, we have potentially repeated measures on individual patients nested within care coordinators who are nested within teams (the unit of randomization) who are in turn nested within region (Australia and the United Kingdom or possibly to be known as Scotland). The analysis will adjust for these factors using appropriate random (service user, if relevant; care coordinator; and team) and fixed (region) effects. The trial statistician will remain blind until the main analyses are complete. Baseline characteristics of the study population will be summarized separately within each randomized group. Baseline characteristics will also be presented for drop-outs and completers within each treatment group.

A full Health Economic Statistical Analysis Plan will be written before any analysis is being undertaken. As part of the within trial economic evaluation, we propose to test 2 health-related quality of life measures (which can be used to assess Quality-Adjusted Life Years), the EQ-5D-5L, and the AQoL-8D in the feasibility trial. Although the EQ-5D-5L is very commonly used in the United Kingdom and Australian context, its sensitivity and appropriateness in people with schizophrenia has been seriously questioned [74]. The AQoL-8D is a newer HRQoL measure and was developed to be sensitive to the domains of quality of life that are important to people with mental health problems. A RUQ to capture costs incurred will also be tested. This questionnaire will need to be appropriate to both the United Kingdom and Australian context but may require some system-specific modules for services, which differ between the 2 settings.

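### Eight teams leave the team-level ICC very imprecise at 120 or 86 participants, so the claim that the sample suffices to obtain the ICCs is unsupported

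*Protocol article*

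**What the plan says.** The Sample Size section opens with "No formal sample size calculation is appropriate for this pilot phase". It then gives its basis, "The proposed sample size of up to 120 service users across 40 care coordinators in 8 CMHSs", and says that this size "is deemed to be sufficient to establish feasibility and obtain parameters (including the relevant ICCs for the cluster design"). The stated use of those parameters is "to inform the design and size of a future definitive, pragmatic, multicenter, and multinational cRCT".

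The Abstract (Methods) gives the same ceiling: "We aim to recruit up to 120 service user participants from 8 CMHSs". Recruitment and Randomization derives it from "an average of 3 participants per care coordinator (giving a total of up to 120 potential participants"), then reports that, after consultation in May 2018, "these recruitment objectives were amended to 86 participants". That section lists four reasons for the change. It adds that independent methodological and statistical advice held that the feasibility aims would still be met, and that the funders approved. It gives no precision figure and does not mention the ICC.

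Trial Design fixes the number of clusters at 8, with 2 in Melbourne and 6 in Glasgow. Statistical Analysis specifies random effects for care coordinator and team, and "fixed (region) effects".

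**The concern.** The Sample Size section does more than say that ICCs will be reported. It states that the sample is adequate for obtaining them and names sizing the next trial as the purpose. A between-team ICC is estimated from the variation among team means, so the number of teams governs its precision. Eight teams leave 7 degrees of freedom for that variation, and fewer once arm and region are fitted. Adding or removing participants within teams changes little.

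The ICC enters the definitive trial's sample size through the design effect. If a reader takes the sufficiency statement at face value, a pilot estimate near zero would suggest that clustering can be ignored, and a high one that the trial is unworkable. Either could come from the same true value.

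A smaller matter is that the only section justifying the sample size still argues from the superseded target.

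**Working it through.** **Inputs from the article.** 8 teams; 40 care coordinators with 3 participants each on average; original ceiling 120; amended target 86; fixed region effect.

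**Assumptions.** The article states no ICC; 0.05 is the main case, and 0.02 and 0.10 show the range. Team sizes are equal and the outcome is continuous. A one-way ANOVA stands in for the planned nested model, so the care-coordinator level and any repeated measures are ignored. For the design effect, the main trial is assumed to have 15 participants per team.

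**The article's own figure.** 40 × 3 = 120 reproduces. Per team, 120 / 8 = 15 and 86 / 8 = 10.75. The cut is 1 − 86/120 = 28%.

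**Between-team degrees of freedom (df).** 8 − 1 = 7 with only a mean fitted, 6 with arm or region added, and 5 with both.

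**Interval for the ICC.** With m per team and true ICC ρ, set F at (1 + (m − 1)ρ) / (1 − ρ). Divide F by the 97.5% and 2.5% points of the F distribution on (df, N − 8) to get F_L and F_U. Each limit is (F_x − 1) / (F_x + m − 1).

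Worked case, N = 86, ρ = 0.05, 5 df:
- F = (1 + 9.75 × 0.05) / 0.95 = 1.566
- F_L = 1.566 / 2.734 = 0.573, so the lower limit is (0.573 − 1) / (0.573 + 9.75) = −0.04
- F_U = 1.566 / 0.1640 = 9.55, so the upper limit is (9.55 − 1) / (9.55 + 9.75) = 0.44

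The chance of a zero or negative estimate is P(F on (df, N − 8) < 1/1.566), which is 33% here.

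**Results at ρ = 0.05.** Design effect (DE) at the upper limit = 1 + 14 × upper limit.

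| N | df | 95% CI | Estimate ≤ 0 | DE at upper limit |
|---|---|---|---|---|
| 120 | 7 | −0.02 to 0.30 | 21% | 5.2 |
| 120 | 6 | −0.02 to 0.34 | 24% | 5.8 |
| 120 | 5 | −0.02 to 0.40 | 27% | 6.6 |
| 86 | 7 | −0.04 to 0.34 | 28% | 5.8 |
| 86 | 6 | −0.04 to 0.38 | 30% | 6.4 |
| 86 | 5 | −0.04 to 0.44 | 33% | 7.2 |

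A simulation of 20,000 trials with only a mean fitted gave 21% of estimates at or below zero with 15 per team, and 27% with 11 per team.

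**Other assumed ICCs, N = 86.** At 0.02 the interval is −0.05 to 0.28 (7 df) or −0.05 to 0.37 (5 df). At 0.10 it is −0.01 to 0.44 (7 df) or −0.02 to 0.54 (5 df).

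**Would more participants per team help?** Hardly. With 8 teams, 5 df, ρ = 0.05 and 1,000 per team, the interval is still 0.02 to 0.24. A total width of 0.10 at ρ = 0.05 would take about 44 teams of 15 or 64 teams of 10.75 (only a mean fitted).

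**Feasibility proportions.** For retention assumed at 80%, the half-width is 1.96 × √(0.16 × DE / N) with DE = 1 + (m − 1) × 0.05.
- N = 120: DE = 1.70, half-width 9.3 points
- N = 86: DE = 1.4875, half-width 10.3 points

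**The case against.** **The change of target is disclosed.** Recruitment and Randomization gives the date, the bodies consulted, the reasons, the advice and the funders' approval. The 120 is worded as a ceiling. A reader might infer a hidden contradiction or an arithmetic slip; the article supports neither. What remains is a failure to update two places.

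**No recalculation was owed.** The section says a formal calculation is not appropriate for a pilot, so there was none to redo, and the advice behind 86 need not be printed in an article. This stands. The point here concerns a sufficiency statement that the article does make, not a missing power calculation.

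**The text promises no particular precision.** An ICC can be computed from 8 teams, and the wording is only that the parameters will inform the later trial. This stands in part: the statement is optimistic rather than plainly false. But calling the size sufficient for that purpose implies usable precision, and the intervals above are too wide for the pilot ICC to serve as a sizing input by itself.

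**The harm assumes misuse.** A reader might infer that the definitive trial will be sized from the pilot point estimate and so come out far too small. The article nowhere says that the estimate will be used alone, and an analysis plan not shown here may require an interval. That plan cannot add teams, however.

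**The widest figures depend on the df.** An upper limit of 0.44 and a design effect of 7.2 belong to 5 df. With 7 df they are 0.34 and 5.8, and the planned nested model would differ somewhat from either. The range is therefore given, and the conclusion is the same at both ends.

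**Conclusion.** The point holds as an unsupported precision claim of moderate severity. At an assumed ICC of 0.05, the 8-team design leaves values from zero to at least 0.30 open at 120 participants and to at least 0.34 at 86. The chance of a zero or negative estimate is between one in five and one in three. Going from 120 to 86 makes this only modestly worse, because the number of teams is the limit.

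The figures rest on the assumed ICC, equal team sizes, a continuous outcome and the one-way approximation. The imprecision persists across assumed ICCs of 0.02 to 0.10.

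A reader might also infer that the pilot cannot meet its feasibility aims at 86. It can: the half-width for 80% retention grows by one point, and the primary outcomes are feasibility, acceptability, usability, safety and performance.

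**What to change.** 1. In the Abstract (Methods) and the Sample Size section, give 86 as the target and name 120 as the superseded one.
2. Limit the sufficiency claim to the feasibility parameters, such as recruitment and retention proportions. Add that 8 teams give only an imprecise team-level ICC, with the expected interval at 86 and the ICC assumed for it.
3. State that the pilot ICC will be reported with its 95% CI, as supporting information only.
4. State that the definitive trial will be sized over a range of ICCs that includes external values, and not from the pilot point estimate.

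The cost is wording, and a less favourable claim. No further participants, teams or analyses are needed. Although the article reports follow-up complete and the database locked, the change is still useful because the ICC's use in sizing the definitive trial lies ahead.

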### Recruitment and Randomization

The unit of randomization is the CMHS (the cluster). Participating CMHSs will be randomized within stratified pairs to the EMPOWER Relapse Prevention Intervention or to continue their usual approach to care. A statistician at the Centre for Healthcare Randomised Trials (CHaRT) at the University of Aberdeen will provide the allocation codes. The 2 clusters in Australia form a single stratum. The 6 clusters in Glasgow will be paired based on similarity of catchment area in terms of social deprivation or CMHS type (eg, early intervention service).

Researchers will approach each eligible care coordinator and seek their consent to participate in the trial. Before randomization, consenting care coordinators will provide an anonymized list of their current potentially eligible caseload of people using services. This list will then be randomly ordered by CHaRT. Researchers will then approach identified people sequentially in blocks of up to 5 potentially eligible participants and seek informed consent to participate in the study. If there are further participants eligible for inclusion at the end of this block, the researcher will move onto the next block of 5 (if applicable). Care coordinators will provide participants with an easy-to-read information leaflet about the study to enable potential participants to express interest in finding out more information. In Australia, information posters will be displayed within staff areas of participating sites to inform care coordinators of the study and provide contact details of RAs, should they wish to participate.

We aim to approach and consent on an average of 3 participants per care coordinator (giving a total of up to 120 potential participants). Following consultation with the independent Data Management and Ethics Committee (DMEC) and the Study Steering Committee (SSC) in May 2018, these recruitment objectives were amended to 86 participants. This was because of a number of challenges to recruitment including (1) temporary suspension of the study to apply for registration with the MHRA, which delayed start up to recruitment, (2) comprehensive and detailed screening of all potential trial participants, (3) delays arising from care coordinators approaching potential participants, and (4) high rates of turnover among care coordinators. Following independent methodological and statistical advice, there was clear guidance that the original feasibility aims will be met by the trial, and this change to recruitment targets was approved by the funders. After completing baseline assessments on all consenting service users in care coordinators’ and CMHSs’ caseload, the Clinical Trials Unit (CTU) at CHaRT will conduct randomization of the CMHSs. For Australia, with just 2 clusters, this will be by simple randomization by the CTU. For Glasgow, with 6 clusters, the CTU will create 3 pairs of teams based on similarity of the catchment area in terms of social deprivation (Carstairs) score or CMHS type (eg, early intervention service). The CTU will randomly allocate one member of the pair to the intervention, and the remaining member will be allocated to control.

We will explore in this pilot phase the best method of randomly allocating the clusters in the full trial, specifically to establish what matching factors (if any, and/or if matching at all is appropriate, methodologically) are suitable. Any violations of the study protocol will be recorded and reported to the Research Ethics Committee, SSC, and the independent DMEC.

### Statistical Analysis

A full statistical analysis plan will be written before (and published on the CHaRT website) any analysis is being undertaken. All analyses will be carried out using the intention-to-treat principle with data from all participants included in the analysis including those who do not complete the intervention. Every effort will be made to follow up all participants in both arms for research assessments. The analysis will follow the guidelines of the CONSORT statement for clustered randomized trials and recommendations for the analysis of clustered randomized trials when presenting and analyzing the data. Here, we have potentially repeated measures on individual patients nested within care coordinators who are nested within teams (the unit of randomization) who are in turn nested within region (Australia and the United Kingdom or possibly to be known as Scotland). The analysis will adjust for these factors using appropriate random (service user, if relevant; care coordinator; and team) and fixed (region) effects. The trial statistician will remain blind until the main analyses are complete. Baseline characteristics of the study population will be summarized separately within each randomized group. Baseline characteristics will also be presented for drop-outs and completers within each treatment group.

A full Health Economic Statistical Analysis Plan will be written before any analysis is being undertaken. As part of the within trial economic evaluation, we propose to test 2 health-related quality of life measures (which can be used to assess Quality-Adjusted Life Years), the EQ-5D-5L, and the AQoL-8D in the feasibility trial. Although the EQ-5D-5L is very commonly used in the United Kingdom and Australian context, its sensitivity and appropriateness in people with schizophrenia has been seriously questioned [74]. The AQoL-8D is a newer HRQoL measure and was developed to be sensitive to the domains of quality of life that are important to people with mental health problems. A RUQ to capture costs incurred will also be tested. This questionnaire will need to be appropriate to both the United Kingdom and Australian context but may require some system-specific modules for services, which differ between the 2 settings.

### Data Sharing

Data generated by this research will be made available as soon as possible based upon reasonable request to the study chief investigator.

### Ethics Approval

West of Scotland Research Ethics Service (GN16MH271 Ref: REC/16/WS/0042) and Melbourne Health (HREC/15/MH/344).

## Results

Recruitment to the trial began in September 2017, and follow-up of participants was completed in July 2019. The database lock was in July 2019, followed by analysis and disclosing of group allocation.

## Discussion

Relapse among people with a diagnosis of schizophrenia is a major contributor to poorer outcomes in terms of greater symptom severity, distress, and risk of a range of adverse outcomes including coercion into care, self-harm, and suicide [8-12]. People diagnosed with schizophrenia worry about relapse, and this is linked to feelings of anxiety, shame, depression, and shorter time to relapse [18]. Relapse contributes to carers’ experiences of distress and worry and has been linked to greater needs for continuity of communication with mental health care professionals [75]. Mental health staff are concerned about the impact of relapse on service users and carers, but the impact on their roles are also considerable in terms of responding to crises and increased risk [24]. These sources of strain place relationships under significant pressure, which can break down communication, anticipatory care, and shared decision making especially in the context of EWSs of relapse. This can potentially result in loss of collaboration, increased risk of disengagement, and greater use of coercion, thus confirming many of the fearful and threat-based expectations held by service users, carers, and, arguably, the staff [25].

On the basis of our theoretical model outlined earlier, we have developed an intervention that blends a digital intervention with peer support, with triage of increased risk of relapse to prompt early interventions that are attuned to needs of service users. Our approach uses digital technology to enable service users to monitor the *ebb and flow* of emotional well-being in daily life and utilizes an algorithm to deliver messages to enhance attunement, awareness, curiosity, and self-management in response to changes in well-being. In our theory, the blending of digital with peer support is important to cultivate helpful conversations to promote greater autonomy, empowerment, and recovery. We anticipate that conversations focused around the *ebb and flow* of changes in well-being in daily life can also increase opportunities for earlier help seeking, collaboration, and shared decision making in the event of possible EWSs facilitated by clinician triage into a relapse prevention pathway embedded in mental health services.

The EMPOWER trial will deliver the protocol for a blended digital intervention and will establish the feasibility of running a definitive cRCT. We will establish the safety, acceptability, usability, and performance parameters of the EMPOWER intervention. We will learn how to optimize the identification, consent, and follow-up of potentially eligible participants. We will establish the feasibility of measuring and collecting our candidate primary, secondary, and mechanistic outcomes. However, in its own right, our study has a number of important broader implications for digital health interventions for people diagnosed with schizophrenia and psychosis. Our mobile phone app will be available for people to use for up to 1 year on a daily basis. To our knowledge, this will be the longest RCT of a mobile phone app in psychosis to date. In addition, the algorithm that underpins the assessment of *ebb and flow* is, to our knowledge, the first mental health app to be registered as a medical device trial (CI/2017/0039) by the United Kingdom’s Medicines and Healthcare products Regulatory Agency.

We will also establish and report the rater reliability of our a priori definition of relapse that has been informed by our theoretical model [18] that underpins the intervention. In studies of relapse in schizophrenia, there is a lack of consensus as to the definitions of relapse measurement [76], very often studies actually fail to report their definitions of relapse [77], and, to our knowledge, none have ever consulted people with lived experience of psychosis on how relapse is measured and defined. Our approach to relapse assessment aims to address these major shortcomings in the literature making the theory, rationale, measurement, and interrater reliability of our definition explicit. In addition, our approach will enable us to report time to relapse, severity of relapse, and mean severity scores across groups at each follow-up timepoint.

